## 2. Materials and Methods

### 2.1. Study Design

This crossover design randomised controlled clinical trial will include two intervention arms (BFR and sham BFR) with three assessment time points (baseline, immediately after BFR training, and at the end of the shoulder girdle exercise loading session) (Figure 1). Outcome measures assessment during the first (DAY 1) and the second session (DAY 2) will be performed by a blinded independent assessor to the intervention (sham BFR or BFR) to avoid the risk of “data collection ascertainment bias”.

All participants will be blinded to the group allocation to avoid the risk of “expectation bias” and “patient ascertainment bias” [27]. To achieve this, they will be informed that the effect of two different BFR occlusion protocols on pain perception after a low-load resistance exercise bout will be evaluated. The physiotherapists performing the interventions (BFR or Sham BFR) will not be blinded; however, they will not participate in the outcome assessment and will be blinded to the recorded values.

All participants will have an introductory baseline assessment. They will be asked to fill out questionnaires on sociodemographic characteristics, symptoms, comorbidities, and functional limitations. Subsequently, measurement of pain pressure thresholds (PPTs), administration of the Shoulder Pain and Disability Index (SPADI), measurement of maximal voluntary isometric contraction (MVIC), assessment of pain during active abduction, and maximal pain in shoulder external rotation on the numeric pain rating scale (NPRS) will be recorded. Then, participants will be randomly allocated to one of the two intervention groups (BFR and Sham BFR) and will be asked to perform one exercise with BFR. Immediately after the BFR session, they will be asked to evaluate the level of difficulty or exertion experienced during the BFR or Sham BFR exercise using the Borg CR1O scale [28]. Simultaneously, measurement of PPTs, MVIC, and maximal pain during external rotation, pain during active shoulder abduction, and perception of improvement or worsening of symptoms will be recorded. Finally, the participants will be asked to perform the shoulder girdle loading protocol, and a final assessment of the same outcome measures will be performed.

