The participants will be crossover randomised, and the testing sessions will be at least 72 h apart to ensure that their clinical status (pain and other symptoms) has not changed. More specifically, they will be asked: “Has your clinical situation changed since last time?” If their answer is no, they will continue with the rest of the procedure; otherwise, they will be excluded from the second session, and this will be reported. This RCT is registered in ClinicalTrials.gov (Registration number: NCT05956288), and the study was designed according to the Consolidated Standards of Reporting Trials (CONSORT) guidelines for randomised clinical trials [29].

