The primary outcome used to calculate the required sample size using G* Power (v 3.1) software was pain. The sample size calculation was based on a previous study that reported an effect size of d = 0.6 for differences in the NPRS between groups after the BFR exercise [26]. To achieve 95% power at an alpha level of 0.05, 20 patients per intervention for 3 assessment periods of outcome measures are required. Given the crossover design of the study and the possibility that the status of the participants will change between the first and the second intervention, it is estimated that there will be a dropout of 20%, and thus, it is proposed to recruit 24 participants per group into the study, or 48 participants in total.

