### 2.7. Statistical Analysis

Descriptive statistics will be used to present and describe participant characteristics (values will be presented as mean and standard deviation or median and interquartile range).

The residuals of each variable/model will be tested for normality by visual inspection of frequency histograms and Q–Q plots [59] or by using the Shapiro–Wilk test [60]. Mixed-effects models will be constructed considering the primary outcome measures (PPTs, MVIC, and maximal pain during external rotation) using participant random effects for all assessment time points. Fixed effects will include the day of assessment (DAY 1 or DAY 2), the two treatment groups (BFR and sham BFR), the time points of assessment of the outcome measures, and all interactions. Additionally, we will model parameter estimates for variables associated with pain responses, such as age, height, and condition chronicity. If a statistically significant effect or interaction is found, we will perform a post hoc test using Tukey’s adjustment for multiple comparisons. Statistical analyses will be conducted using JMP (v.16.0, SAS Corporation, Cary, NC, USA), and the statistical significance will be set at α = 0.05.

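### The stated mixed model has participant random effects but no session term, so if participants vary from day to day the standard error is too small for the treatment main effect and too large for the BFR-sham difference in within-session change

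*Protocol article*

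**What the plan says.** Section 2.7 of the protocol article describes the random part of the model for PPTs, MVIC and maximal pain in external rotation as "using participant random effects for all assessment time points". The fixed part is stated too: "Fixed effects will include the day of assessment (DAY 1 or DAY 2), the two treatment groups (BFR and sham BFR), the time points of" (the sentence goes on to name the measurements and to add every interaction among these terms). No participant-by-day term and no residual covariance structure is named. After any significant effect or interaction, "we will perform a post hoc test using Tukey’s adjustment for multiple comparisons".

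Section 2.1 gives the data structure: "three assessment time points (baseline, immediately after BFR training, and at the end of the shoulder girdle exercise loading session". These are taken in each of two sessions, and "the testing sessions will be at least 72 h apart". Each participant therefore contributes 2 × 3 = 6 values per outcome, three under each treatment.

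**The concern.** The treatment changes between days, not within a day, so for treatment the experimental unit is the session. A participant who happens to be more tender or weaker on one day will tend to be so at all three assessments that day. The fixed day effect removes only the average shift between the two days. It does not remove each person's own deviation.

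A model with a participant effect alone treats all six values as equally correlated. Contrasts that compare whole sessions then look more precise than they are, and contrasts of change within a session look less precise. Both matter here: a significant treatment effect opens the post hoc comparisons, while the objective (less pain after BFR, maintained after loading) is a question about change.

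Session variance above zero is plausible on the protocol's own account. Section 2.3 allows for 20% dropout partly because clinical status may change between interventions, and PPT and force are taken with hand-held instruments.

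**Working it through.** **The plan's own figure.** Section 2.3 uses a prior study that "reported an effect size of d = 0.6 for differences in the NPRS between groups after the BFR exercise", with 95% power and alpha 0.05, and arrives at 20 per intervention (40 in total), then 24 per group. The test is not named. A two-sided paired t-test with d = 0.6 needs 39, and 40 gives 95.9% power; 20 × 1.2 = 24. That sample size does not use the mixed model, so this point leaves it unchanged.

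**Set-up.** Let each value be participant + session (variance s²) + residual (variance e²), and let L = s²/(s² + e²). L is not in the documents. I take 0.1, 0.3 and 0.5 as an assumed range, with s² + e² = 1.

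**Residual under a participant intercept alone.** Each participant has 5 within-participant degrees of freedom: 1 between sessions (expected mean square e² + 3s²) and 4 within sessions (e²). Pooled: (e² + 3s² + 4e²)/5 = e² + 0.6s².

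**Variance of each contrast, per participant.**
- Treatment main effect: true (2/3)(e² + 3s²); model (2/3)(e² + 0.6s²).
- BFR-sham at one time point: true 2(e² + s²); model 2(e² + 0.6s²).
- BFR-sham difference in change: true 4e²; model 4(e² + 0.6s²).

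**Ratio of model SE to true SE**, with two-sided type I error 2Φ(−1.96 × ratio) in brackets:

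| L | Main effect | One time point, unadjusted | Difference in change |
|---|---|---|---|
| 0.1 | √(0.96/1.2) = 0.89 (8.0%) | √(0.96/1) = 0.98 (5.5%) | √(0.96/0.9) = 1.03 (4.3%) |
| 0.3 | √(0.88/1.6) = 0.74 (14.6%) | √(0.88/1) = 0.94 (6.6%) | √(0.88/0.7) = 1.12 (2.8%) |
| 0.5 | √(0.80/2.0) = 0.63 (21.5%) | √(0.80/1) = 0.89 (8.0%) | √(0.80/0.5) = 1.26 (1.3%) |

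At L = 0 every ratio is 1. Simulation with 40 participants, the full fixed-effects factorial and 20,000 runs agrees: at L = 0.3 the main effect rejects in 14 to 15% of runs and the difference in change in just under 3%; at L = 0.5 in 21% and about 1.5%.

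**Power of the change contrast.** If it has 95% power under the correct SE, it has Φ(3.605 − 1.96 × ratio) under the participant-only model: 94%, 92% and 87%.

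**With the planned Tukey adjustment.** Over the six treatment-by-time cells the critical t is about 2.88. At L = 0.5 one BFR-sham comparison has type I error 2Φ(−2.88 × 0.894) = 1.0%, against a nominal 0.4%. In simulation the chance of a false positive in any of the three is about 3% at L = 0.5 and about 2% at L = 0.3, without requiring a significant effect first.

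**Adding a session effect.** In REML fits at L = 0.3 with 40 participants, the mean SE at one time point moves from 0.210 to 0.225 (true 0.224), and that of the difference in change from 0.297 to 0.263 (true 0.265).

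**The other reading of the wording.** If participant-by-time effects are meant, the residual pools over 3 degrees of freedom: (e² + 3s² + 2e²)/3 = e² + s². The single-time-point variance is then right, provided that the participant-by-time variance is at least s²/2 (below that its estimate falls to zero and the table above applies). At L = 0.5 the main effect ratio is √(1/2) = 0.71 (about 17% type I error), and the change SE is √2 = 1.41 times its true value.

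**The case against.** **The wording is loose, and this is an article.** The phrase is plural and tied to time points, and it does not say that only a random intercept is used. Nesting and covariance details are often left to a fuller document. This stands in part: under the participant-by-time reading the single-time-point contrast can be correct. But the article does state the random part and puts day among the fixed effects. On neither reading is there a session term, and the main effect and change contrast remain mis-scaled on both.

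**The largest error is not in the contrast of interest.** The treatment main effect averages in each session's pre-treatment baseline, so it does not answer the objective. The treatment-by-time contrast does, and there the error is conservative. This stands. A reader might take 21% as the false-positive risk of the trial's main conclusion; the documents do not support that.

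**The post hoc tests are adjusted.** A reader might infer from the unadjusted 5.5 to 8% that the BFR-sham comparisons at each time point exceed 5%. With the planned Tukey adjustment they do not. Their standard errors are still 2 to 11% too small under the participant-intercept reading.

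**The size is unknown.** No document gives the session variance, and section 2.1 removes from session 2 anyone who reports a changed clinical situation. That limits day-to-day variation, but a single yes/no question cannot remove the ordinary part of it. The test-retest ICC of 0.92 to 0.98 in section 2.6.2 does not settle the matter: it sets error against the spread between participants rather than against within-session residual variance, and it covers MVIC only.

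**The 95% power is borrowed.** Section 2.3 does not say that its 95% is power for a difference in change. The 94%, 92% and 87% therefore illustrate the loss; they do not restate the trial's power.

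**Conclusion.** The concern holds in limited form. As written, the model omits participant-by-day variation in a design where treatment is given by day. If that variation is above zero, the main effect test is anti-conservative, materially so even at a session share of 0.1. The change contrast that answers the objective is conservative, with a small to moderate loss of power. The single-time-point error is small, depends on how the wording is read, and stays below 5% after Tukey adjustment.

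The results rest on an assumed range for the session share, a balanced 2 × 3 layout, normal errors and the participant-intercept reading, except where the other reading is stated. If there is no session variance, the model is correct. This is something that should be fixed, not a fault that invalidates the trial. Confidence is good for the direction of the errors and moderate for their size.

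**What to change.** In section 2.7, add a participant-by-day (session) random effect nested in participant, or a covariance structure that allows higher correlation within a day than between days, with Kenward-Roger degrees of freedom. State that the conclusion rests on the treatment-by-time contrast, that is, the BFR-sham difference in within-session change, and not on the treatment main effect.

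The cost is a line or two of text and one extra variance component. Intervals for between-session contrasts become slightly wider; those for within-session change become narrower when session variance is present. No new data are needed and the stated sample size does not change.

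### No BFR-versus-sham contrast is named as the test of the objective: any significant model term opens Tukey tests, baseline dilutes the treatment main effect, and the sample size makes no allowance for Tukey

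*Protocol article*

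**What the plan says.** The Introduction asks two things: whether one BFR bout reduces pain compared with sham, and whether any reduction survives the shoulder loading session that follows.

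Section 2.1 sets "three assessment time points (baseline, immediately after BFR training, and at the end of the shoulder girdle exercise loading session", so the first of the three measurements precedes treatment.

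Section 2.7 puts all three time points into mixed models with participant random effects. The fixed effects are day, "the two treatment groups (BFR and sham BFR), the time points of assessment of the outcome measures, and all interactions". The decision rule is "If a statistically significant effect or interaction is found, we will perform a post hoc test", adjusted by Tukey's method, and "the statistical significance will be set at α = 0.05". No term or contrast is singled out as the test of the objective.

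Section 2.3 bases the sample size on "an effect size of d = 0.6 for differences in the NPRS between groups after the BFR exercise" and states "To achieve 95% power at an alpha level of 0.05, 20 patients per intervention for 3 assessment periods of outcome measures are required". After an allowance of 20% for dropout, "it is proposed to recruit 24 participants per group into the study, or 48 participants in total".

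**The concern.** Only the BFR-minus-sham differences at pre-loading and post-loading answer the question. The stated rule does not point to them.

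- **The trigger is too wide.** Seven terms can open the post hoc step, including a day effect or a time effect, neither of which concerns BFR. Day-by-treatment is also a trigger. In a two-period crossover, the treatment given on a particular day is fixed by the sequence, so this interaction is aliased with sequence and carryover and is not evidence of efficacy.
- **The treatment main effect is diluted.** It averages in a time point at which no effect can exist.
- **Sizing and analysis do not match.** The effect size describes one post-exercise difference, but the conclusion may rest on a Tukey-adjusted pair.

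At stake are an effect of the planned size being missed, and a choice of which comparison to report being made after the data are seen.

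**Working it through.** **Inputs.** From Section 2.3: d = 0.6, power 95%, 20 per intervention (40 in total), 48 recruited, 20% dropout. From Section 2.7: α = 0.05 and a day (2) × treatment (2) × time (3) model with all interactions. Assumptions: a two-sided test, and d = 0.6 as the mean paired difference divided by the SD of paired differences. Section 2.3 names neither the test nor the standardisation. Correlations are not given, so a range is shown.

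**1. The plan's own figure.** For a paired t-test the noncentrality is 0.6 × √n with n − 1 degrees of freedom.
- n = 38: 0.6 × √38 = 3.70, critical t 2.03, power 95.0%.
- n = 40: 0.6 × √40 = 3.79, critical t 2.02, power 95.9%.

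The smallest n that reaches 95% is 39, against 40 stated. Then 40 × 1.2 = 48, and 48 × 0.8 = 38.4, so about 38 to 40 completers. The stated figure is reproduced on this reading. Read instead as a comparison of two independent groups, 20 per group would give only about 46%.

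**2. Terms and cells.** Three main effects, three two-way interactions and one three-way interaction make 7 terms. Treatment by time has 2 × 3 = 6 means and 6 × 5 / 2 = 15 pairs. If all seven terms were null and independent, at least one would be significant with probability 1 − 0.95⁷ = 30%.

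**3. Dilution by baseline.** Let δ be the effect at a post-treatment time point.
- Sustained effect: (0 + δ + δ)/3 = 2δ/3.
- Effect only just after the bout: (0 + δ + 0)/3 = δ/3.

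This needs no assumption beyond equal weighting of the three times. What it does to power depends on the correlation r between the paired differences at the three times, because the SD of their average is √((1 + 2r)/3) times the SD of one. Main-effect power with n = 38:

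| Effect | r = 0 | r = 0.5 | r = 1 |
|---|---|---|---|
| Sustained | 98.6% | 84% | 67% |
| Only just after the bout | 55% | 31% | 22% |

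**4. Cost of Tukey, with no baseline term involved.** The critical value is q(0.95; 6, df)/√2 with df = 5(n − 1), about 2.88 in place of about 2.02.

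| Completers | One planned contrast | Within the six-mean Tukey family |
|---|---|---|
| 38 | 95.0% | 79.2% |
| 40 | 95.9% | 81.9% |
| 48 | 98% | 90% |

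A simulation of the random-intercept model (20,000 runs) gave 79.7% and 82.0% for the Tukey column at 38 and 40. Restoring 95% within that family would take about 57 completers. With two means, Tukey's test is the t-test and costs nothing.

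**The case against.** The strongest reply is that Section 2.7 does not say every pair of cells is compared whenever any term is significant. Following up only the significant term is an equally natural reading. A significant day effect would then lead to a two-level comparison of days, and a significant treatment effect to a two-level comparison that Tukey does not penalise. Tukey also controls its own family's error without a gate, so the 30% in step 2 is not a rate of false claims about BFR. Treatment by time is already in the model, so the useful contrasts can be obtained. Section 2.3 mentions three assessment periods, which may point to a repeated-measures calculation.

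Much of this stands. The power loss is conditional on which term is followed up, and the 95% to 96% starting point is a reading of Section 2.3. But the one follow-up that avoids the Tukey cost is the main effect that baseline dilutes, and the text does not restrict follow-up to it. The rule is written into the plan, so this is more than detail deferred to a later document.

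A reader might go further in three ways that the documents do not support:

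- **Power falls to about two thirds.** Putting the critical value for all 12 day-by-treatment-by-time means on the full-sample contrast gives 65% to 69%. That contrast is not a pair in that table, where each cell holds half the participants. The figure describes no planned comparison.
- **Counting baseline causes the power loss.** The fall in step 4 comes from Tukey alone. For a sustained effect the main effect can even gain power (98.6% at r = 0).
- **A baseline-adjusted contrast is assured of 95%.** The correlation with baseline is not given. A plain change from baseline with r = 0 has twice the variance and 72% to 74% power at 38 to 40 completers.

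**Conclusion.** The point holds in a limited form. The plan names no BFR-versus-sham contrast as the test of its objective and lets any significant term open post hoc testing. The treatment main effect understates a sustained effect by one third and an immediate-only effect by two thirds. That is a shrinkage of the estimate, and its effect on power cannot be fixed from the documents.

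Separately, the sample size carries no allowance for Tukey. The cost is a fall from about 95–96% to about 79–82% with 38 to 40 completers, or to about 90% if all 48 complete. This rests on d = 0.6 being a standardised paired difference, a two-sided test, and follow-up covering all six treatment-by-time means. It is zero if only the two-level main effect is followed up. The plan should be changed because the remedy is cheap, but the trial is not invalid as it stands.

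**What to change.** In Section 2.7, replace the trigger rule with two prespecified contrasts: BFR minus sham at pre-loading, then BFR minus sham at post-loading. Test them in that order at 0.05, the second only if the first is significant, with no omnibus gate and no Tukey adjustment. Use the post-treatment values as the response, the same session's baseline as covariate, and day as a fixed effect. State that day-by-treatment terms are not efficacy triggers. Keep Tukey for exploratory pairs. In Section 2.3, say which contrast d = 0.6 refers to and how it is standardised.

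The order follows the objective: an immediate effect first, then its maintenance. The change costs wording only, with no extra participants or measurements, since each session's baseline is already collected. The downside is that all other pairwise comparisons become descriptive.

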Blood flow restriction training (BFR) is a type of exercise with parallel partial restriction of the arterial inflow and complete venous outflow restriction in the muscle tissue that is usually combined with parallel execution of low-load resistance exercise loading. Blood flow restriction is achieved by using inflatable cuffs applied to both the upper and lower extremities [16,17]. During the last decade, the popularity of this technique seems to have grown rapidly due to its beneficial effects on increasing muscle strength and muscle hypertrophy in healthy adults [18,19,20] and clinical populations [21,22], as well as its acute hypoalgesic effect on the healthy population by significantly increasing the patient pain threshold [23,24,25]. However, to date, only one published study has examined the acute hypoalgesic effect of BFR training in a clinical population, showing beneficial adaptations in reducing pain in people with patellofemoral pain [26].

The primary objective of the present study is to evaluate whether a combination of a single acute BFR with a low-load exercise bout would reduce pain perception in patients with nonspecific shoulder pain and whether the potential hypoalgesia would be maintained after a 45 min physical therapy shoulder exercise loading session. The BFR exercise protocol will be compared to a sham BFR exercise protocol. We hypothesise that the participants in the BFR group would experience reduced pain perception and would be able to complete a scapula and rotator cuff muscle loading program with reduced pain.

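### Section 2.7 names no BFR-minus-sham contrast; if its Tukey step spans the six treatment-by-time cells, power for the post-BFR comparison falls from about 96% to about 82%

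*Protocol article*

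**What the plan says.** The Introduction sets two questions: whether one low-load BFR bout lowers pain compared with sham, and "whether the potential hypoalgesia would be maintained after a 45 min physical therapy shoulder exercise loading session".

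Section 2.3 bases the sample size on an earlier study that "reported an effect size of d = 0.6 for differences in the NPRS between groups after the BFR exercise". It continues: "To achieve 95% power at an alpha level of 0.05, 20 patients per intervention for 3 assessment periods of outcome measures are required". With 20% dropout this becomes 24 per group, 48 in all.

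Section 2.7 fits mixed-effects models with a participant random effect. The fixed effects are day (two levels), treatment (two), time point (three) and all their interactions. The decision rule is: "If a statistically significant effect or interaction is found, we will perform a post hoc test using Tukey’s adjustment for multiple comparisons". On the error level it says only that "the statistical significance will be set at α = 0.05".

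The section does not say which term, time point or BFR-sham difference decides the question, or which pairs the Tukey adjustment covers.

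**The concern.** The sample size points to a BFR-sham difference in pain after the BFR exercise. The analysis rule does not test that difference by name. It waits for some significant term, which may have nothing to do with treatment, and then makes multiplicity-adjusted pairwise comparisons.

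With two treatments and three times there are six treatment-by-time cells and 6 × 5 / 2 = 15 pairs. Only two of those pairs answer the stated questions: BFR against sham at pre-loading, and BFR against sham at post-loading. If Tukey covers all 15, these two pay for 13 others, such as baseline against baseline or one time against another within an arm. Section 2.3 does not budget for that. At stake is a real effect of the planned size being missed more often than the stated 95% power implies.

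**Working it through.** **Inputs.** From section 2.3: d = 0.6, alpha 0.05, power 95%, 20 per intervention, 48 recruited. From section 2.7: 2 treatments × 3 times = 6 cells.

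**Assumptions.** The test is two-sided. The 20 per intervention means 40 evaluable people (20 per sequence). The 0.6 is a paired standardised effect. The covariance follows the plan's own participant random effect, with no extra session-to-session variance.

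**1. Reproduce the plan's figure.** For a paired contrast the noncentrality is 0.6 × √n.
- n = 39: 0.6 × √39 = 3.75, power 95.5%.
- n = 40: 0.6 × √40 = 3.79, power 95.9% (96.5% with the mixed model's 190 residual df).
- n = 48: 0.6 × √48 = 4.16, power 98.3% (98.5% with 230 df).

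So 40 evaluable fits the stated 95% for one unadjusted contrast.

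**2. Apply Tukey over six cells.** The critical t is the studentized range quantile divided by √2.
- n = 40, 190 df: 4.07 / √2 = 2.88, against 1.97 unadjusted. Power is 82%.
- n = 48, 230 df: 4.06 / √2 = 2.87. Power is 90%.
- At n = 40 with other effect sizes, power is 61% for 0.5 and 94% for 0.7.

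**3. Add the gate as written (any significant term).** In a simulation of the crossover (20,000 runs per setting, within-person correlation 0.5, n = 40), gate plus Tukey for the pre-loading contrast gives 81–82%. The gate costs almost nothing, and Tukey causes the loss. The gate also says little about treatment: with a time effect of half a standard deviation and no treatment effect, it opened in over 99% of runs.

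**4. A stricter gate: treatment-by-time must be significant.** For an effect at pre-loading only, the three BFR-sham differences are 0, 0.6 and 0. Their squared deviations from the mean of 0.2 sum to 0.04 + 0.16 + 0.04 = 0.24. The noncentrality is 40 × 0.24 = 9.6 on 2 and 190 df, so the F test alone has 79% power. With Tukey added, simulation gives about 73% if the effect is at pre-loading only and about 68% if it is equally large at post-loading.

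**5. The treatment main effect.** It has two levels and so carries no Tukey penalty, but it averages the difference over baseline, pre-loading and post-loading. Its noncentrality is the mean difference × √(3 × 40).
- Effect at pre-loading only: 0.2 × √120 = 2.19, power 59%.
- Equal effect at both later times: 0.4 × √120 = 4.38, power 99%.

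**The case against.** **The Tukey family is an inference.** Section 2.7 does not say that all cell pairs are compared, and an article-length protocol commonly leaves the list of contrasts to an analysis plan. This stands, so the 82% is conditional on the six-cell family. What remains is that the published rule can be opened by a term unrelated to treatment and identifies no deciding comparison.

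**The sample size may not be for a single comparison.** The reference to three assessment periods could mean a repeated-measures F test. With f = 0.3, three measurements and 40 participants, the treatment-by-time test has about 94–97% power at correlations of 0.30–0.40. This also stands as a possible reading. It does not supply the missing contrast: a significant interaction does not say at which time BFR and sham differ.

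**If the effect persists, the main effect has about 99% power.** That is correct under an equal effect at both later times and no session-to-session variance. But the main effect includes a time point before treatment and cannot separate an initial reduction from one that lasts.

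**Two stronger readings do not hold.** A reader might infer that power generally drops below 75%. That requires treatment-by-time significance as a further condition, whereas the written gate accepts any term. A reader might also infer that the open gate inflates false BFR-sham claims. In null simulations with six-cell Tukey, a false BFR-sham difference at the same time point arises in only about 1.3% of runs for a given outcome.

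**Conclusion.** The point holds as a cheap improvement, not as an error that invalidates the design. Section 2.7 fixes a decision rule that does not name the comparison described in section 2.3, and the sample size carries no allowance for the adjustment.

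Under the assumptions listed (paired d of 0.6, Tukey over six cells), power for BFR minus sham at pre-loading is about 82% rather than 96% with 40 evaluable participants, and about 90% rather than 98% if all 48 are evaluable. The 68–73% range applies only if a significant treatment-by-time interaction is also required. If Tukey were applied only to the two-level treatment term there would be no penalty, but the quantity tested would not be the post-BFR difference.

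**What to change.** In section 2.7, replace the trigger-then-Tukey rule for the BFR-sham question with two contrasts from the same mixed model:

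1. BFR minus sham at the pre-loading assessment, two-sided 0.05, tested whatever the omnibus tests show.
2. Only if the first is significant, BFR minus sham at the post-loading assessment at 0.05, defined as the test of whether the hypoalgesia lasts.

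Report both with 95% confidence intervals, and keep Tukey all-pairs comparisons as exploratory. Under the same assumptions this restores about 96% power for the first contrast with 40 evaluable participants.

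The cost is two sentences, written before the data are analysed, with no added participants or measurements. The small downside is that the other pairwise comparisons become descriptive.

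If the present rule is kept with Tukey over the six cells, section 2.3 should give the power as about 82% with 40 evaluable (about 90% with 48) and state the assumptions.
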